#### **8.2.2.3. Urinary analyses**

Urine samples for albumin and creatinine will be frozen at -80° C at the University of Toronto, in a locked room, in a locked building for analysis. The BBDC at the University of Toronto will perform analyses of the urine albumin and creatine using the Jaffé alkaline picrate method[72].

#### **8.2.2.4. Biomarkers of adherence**

All objective biomarkers of adherence will be assessed at the Department of Nutritional Sciences, University of Toronto and will be conducted using stored serum samples at -80°C. 2% soy milk intake adherence will be assessed by UIE and will be analyzed by liquid chromatography isotope-dilution tandem mass spectrometry (LCMSMS) [42]. 2% cow's milk adherence will be assessed by dairy-derived serum fatty acids, and will be analyzed by serum quantification of four fatty acids: 15:0, 17:0, CLA and TPA[43]. The fatty acids will be extracted as total lipids using the Folch et al. method [73] and they will be separated and quantified using modified methods as described by Abdelmagid et al.[74]. SSBs adherence will be assessed by urinary fructose and sucrose. Urinary fructose and sucrose will be measured by gas chromatography-mass spectrometry (GC-MS)[75].

#### **8.2.3. Dietary Assessment**

Diet quality will be measured with the AHEI using the Harvard Willett FFQ [40] and with the HEI using the online Diet ID [41] platform. We will be using the booklet 07 FFQ, a self-administered questionnaire to assess the intake of various nutrients. Nutrient intakes will be computed by assigning a daily frequency weight. Additionally, participants will be doing a digital assessment of their diets at three time points for the study (week 0, week 12 and week 24) using Diet ID. For this digital assessment, participants will be given a unique code identifier to log into the Diet ID web-based software via a custom study link that will be accessed by all participants for the required timepoints. Diet ID will prompt participants to view a series of food images, each representing unique diet patterns. After choosing the best match, participants then indicate diet preferences and enter biometric data (self-reported height, weight, age, sex, activity level).

#### **8.2.4. Medical Imaging**

For the  $^1\text{H}$ -MRS we will use a 3T Siemens Magnetom Skyra scanner (Erlangen, Germany) with either an 18 channel body phased array coil or a dedicated peripheral phased array coil. Single voxel, 30mm cubed spectroscopy will be acquired for IHCL and IMCL using a STEAM (Stimulated Echo Acquisition Mode) sequence and the following acquisition parameters: TR 3000 ms, multiple TE values 12 ms, 24 ms, 36 ms, 48 ms, 72 ms, mixing time (TM) 10 ms, 10 averages, 1024 data points and receiver bandwidth 1200 Hz for an acquisition time under one minute. Participants will be scanned for 30 minutes. Participants with anxiety and/or claustrophobia, will be given the option to take oral medication to minimize the anxiety.

#### **8.3. Data Integrity/Management**

All paper copies of data forms will be stored under a double lock system to ensure confidentiality (locked cabinet in a locked office). Only PI, co-investigators and assigned study personnel will have access to the cabinet. The participant digital database will be securely stored centrally at SMH. The data management system enables anonymized and secure information storage, retrieval and sharing and will be organized and supported by the Li Ka Shing Knowledge Institute IT team of St. Michael's Hospital. All data forms will be stored under a double lock system to ensure confidentiality. Only the PI, co-investigators and assigned trial personnel will have access to the cabinet. The AHRC, St. Michael's Hospital, will be contracted to manage the digital database securely and ensure data integrity. Their data management system enables anonymization, secure information storage, retrieval, and sharing of data.

##### **8.3.1. Personal Health Information**

We will be collecting personal health information during this study. The personal health information will include name, phone number, email address, demographic information, health history, questionnaires and records, and research visit records. In order to keep participant data confidential, we will create a master linking log which will separate identifying data (name and contact information) from study data with a study ID. The master linking log will be kept in a password-protected file on a drive through St Michael's Hospital computer, only accessible to study staff and investigators. Any subject requesting access to their personal health information will be able to do so by requesting this through the study coordinator.

##### **8.3.2. Trial facts**

Potential participants will see the advertisement for the study and their participation will be voluntary. If they choose to participate in the survey, they will be asked for personal information such as complete name, email address, and contact number. If potential participants decide to continue, they will be asked to respond to questions regarding the study eligibility criteria. At any point, the potential participant will have the opportunity to stop the survey before completing it, and any information used

up to that point will not be used. However, if the potential participant completes the survey, they will be giving their consent to us to collect their answers to the survey, including their contact information. While completing the survey they will have the option to join the mailing list to be contacted via email about future clinical trials for which they might be eligible. Trialfacts comply with the Privacy Act 1998 (Cth) (Privacy Act) and specifically the Australian Privacy Principles (APP). In addition, they comply with the HIPAA (Privacy Rule which is the primary protection regime under US law and applies to personal health information) and PHIPA (Personal Health Information Protection Act which is the Ontario's health privacy legislation). Trialfacts will delete the information from their records upon the potential participants' request or will de-identify personal information once it is no longer needed for a valid purpose or required to be kept by law.

### **8.3.3. Honeybee**

Potential participants will see the advertisement for the study and their participation will be voluntary. If they choose to participate in the survey, before they start the survey they will be prompted to log in to their existing Honeybee account if they have one, to create a new Honeybee account or to skip the survey and contact the STEM trial team directly via email. They will be asked for personal information such as complete name, email address, and contact number. If potential participants decide to continue, they will be asked to respond to questions regarding the study eligibility criteria. At any point, the potential participant will have the opportunity to stop the survey before completing it, and any information used up to that point will not be used. However, if the potential participant completes the survey, they will be giving their consent to us to collect their answers to the survey, including their contact information. Participants with a Honeybee account will have the option to opt-in to receive Honeybee newsletters which relays other relevant clinical trial or health studies to them based on their profile information. Honeybee is an entirely HIPAA and PIPEDA (Personal Information Protection and Electronic Documents Act) compliant platform. Honeybee will delete the information from their records upon the potential participants' request or will de-identify personal information once it is no longer needed for a valid purpose (audits, to ensure data integrity) or required to be kept by law.

### **8.3.4. Diet ID**

No personal identifying information will be shared with this company. Instead of names or email addresses, a study ID will be used. Data received and processed by Diet ID includes gender, age, height, weight, activity level, and nutrient analysis. The data will be housed external to St. Michael's Hospital within the Diet ID app server, Aptible, which is a HIPAA compliant hosting service that runs on AWS (Amazon Web Service). The study team will be provided access to the admin dashboard and will be able to log in with administration credentials and view/export limited participant data. The complete data export can be exported by an assigned administration staff. Administration staff will have a username and password that includes 2-step verification. Study data will be kept in a password-protected file on a drive through St. Michael's Hospital computer, only accessible to study staff and investigators.

## **8.4. Subject Compensation**

Once a participant is randomized, travel compensation will be provided. To compensate for time required for study visits, each participant will be compensated a total of \$350, which will be divided into

3 payments: \$100 at beginning of the trial (week 0), \$100 in the middle of the trial (week 12) and \$150 at completion of the trial (week 24). Transportation costs (i.e. parking or TTC tokens) will be reimbursed (up to \$25 per visit) and breakfast will also be provided at each study visit. Any transportation costs incurred for additional visits for obtaining fecal and urine collection kits will be reimbursed as well.

## **8.5. Anticipated Challenges**

### **8.5.1. Recruitment challenges**

We require individuals who are regular SSB drinkers. In fact, soft drinks are the second largest source of added sugars for adults in Canada [76] and the per capita intake of SSBs in Canada is 0.9 with estimated 20 percent drinking more than 1 SSB serving per day [77], there is estimated 10 percent adult population that drinks more than 1 SSB serving per day. We plan to recruit from overweight and obese individuals who are known to have a higher SSB intake [78]. In addition, there are new challenges due to COVID-19 restrictions.

### **8.5.2. Compliance challenges**

In dietary studies, compliance is usually a challenge. We will address this by having participants keep beverage logs during the trial. Beverages will be provided to the participants from the study site for the first week of each visit and shipped via Starhawk express for the three subsequent weeks. In addition, adherence to treatment will be reinforced with regular phone calls and/or emails to the participants.

## **9. Incidental findings and incident diabetes**

*An incidental finding is a finding concerning an individual research participant that has potential health or reproductive importance and is discovered in the course of conducting research but is beyond the aims of the study [79].* Any incidental findings (as defined above) obtained during the course of the main study from laboratory tests or HMRs studies will be provided to the family physician for further investigation. Participants will be notified in reassuring terms and advised to follow-up with their family physician. If a participant does not have a family physician at the time of diagnosis, then specialist referrals will be made as necessary. If genes identified have clinical implications the advice of experts in that particular field will be sort to arrange appropriate counseling for the participant. The family physician's involvement would be sought if the participant consents to it. However, the chances of incidental findings are limited since only specific genes known to affect dietary response will be studied.

## **10. Banking of Samples**

Blood samples (de-identified) will be stored at the University of Toronto (at the Medical Science Building) until all planned analyses have been undertaken-usually about 3 to 5 years. Longer-term banking storage for all samples will be 30 years after study completion to allow for use in future secondary and exploratory analyses in relation to the objectives of the current research project. At the

end of each storage period, samples will be destroyed by autoclaving. Presently the use and ultimate destruction of these samples will be the responsibility of the investigator, [name].

Secondary, exploratory, and adherence outcomes will be assessed by superiority testing among the active treatment (2% soy milk), reference treatment (2% cow's milk), and control treatment (SSB). By reporting all estimated effects and confidence intervals with p-values, the necessary context is provided for a proper interpretation of the statistical evidence [<https://www.tandfonline.com/doi/full/10.1080/00031305.2016.1154108>]. If it is required for a future regulatory submission, then the secondary outcomes will be adjusted for false discovery. The approach will depend on the results of the primary outcome. If the superiority testing of the primary outcome is significant, then we will analyze the secondary outcomes using the Benjamini-Hochberg false discovery rate controlling method with a starting alpha of 0.05 to correct for false discovery [80].

The sample size was selected to allow sufficient power for this analytical approach. The primary analysis will be conducted according to the intention to treat (ITT) principle with IPW to account for any missing values. Data will be analyzed using ANCOVA models for continuous data (mean differences with 95% CIs) and logistic regression models for categorical data (odds ratio with 95% CI for MetS reversion and relative risk with 95% CI for diabetes incidence). Adjustments will be made for age, sex, NAFLD status, medication use, intervention dose (servings/day), and baseline level of the end value. Sensitivity analyses will include completers, per protocol analyses, and ITT with MI.

Prespecified subgroup analyses will be conducted using Chi-square tests by age, sex, NAFLD status, caffeinated beverage use (cola vs non-cola drinkers), intervention dose (servings/day), and baseline waist circumference, FPG, 2hPG, Triglycerides, HDL-C, BP. Continuous linear (dose response gradient) and non-linear (dose response threshold) dose-response analyses will be undertaken over the natural dose response range (3, 4, 5, or 6 servings per day) by multiple linear regression and piecewise regression analyses, respectively.

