| Study Population:                                                                              | Overweight/obese participants with MetS who are consuming $\geq 1$ SSBs/day                                                                                                                                                                                                                                                                                                                                                                                                                                                                                                                                                                                                                                                                                                                                                                                                                                                                                                                                                                                                                                                                                                                                           |

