|--------------------------------------------------------------------------------------------------------------------------------------------------|-----------------------------------------------------------------------------------------------|------------------------------------------------------------------------------------------------------------------------------------------------------------------------------------------------------------------------------------------------------------------------------------------------------------------------------------------------------------------------|
| To assess the effect of using 2% soy milk versus 2% cow's milk to replace SSBs on SBP in overweight/obese participants with MetS.                | MetS criteria (SBP)                                                                           | 
 
2% soy milk and 2% cow's milk intake will each result in significant SBP reduction compared to SSBs intake in overweight/obese participants with MetS.
 
2% soy milk intake will show to be non-inferior to 2% cow's milk intake on SBP reduction in overweight/obese participants with MetS.
 
                 |
| To assess the effect of using 2% soy milk versus 2% cow's milk to replace SSBs on DBP in overweight/obese participants with MetS.                | MetS criteria (DBP)                                                                           | 
 
2% soy milk and 2% cow's milk intake will each result in significant DBP reduction compared to SSBs intake in overweight/obese participants with MetS.
 
2% soy milk intake will show to be non-inferior to 2% cow's milk intake on DBP reduction in overweight/obese participants with MetS.
 
                 |
| To assess the effect of using 2% soy milk versus 2% cow's milk to replace SSBs on MetS reversion in overweight/obese participants with MetS.     | MetS reversion (defined as a reversion to <3 of 5 IDF/NHLBI/AHA/WHF/IAAS/IA SO criteria [37]) | 
 
2% soy milk and 2% cow's milk intake will each result in significant MetS reversion compared to SSBs intake in overweight/obese participants with MetS.
 
2% soy milk intake will show to be non-inferior to 2% cow's milk intake on MetS reversion in overweight/obese participants with MetS.
 
               |

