- Participation in any trials within the last 3 months or for the duration of this study
- Any condition or circumstance which would prevent you from having an MRI (e.g. pacemaker, neurostimulators, breast tissue expanders, implants, or foreign metal object in body)
- Individuals planning on making dietary or physical activity changes throughout study duration
- If self-reported medication use, it must be at a stable dose for  $\geq 6$  months.

\*Disease exclusions will be based upon self-reported diagnosis

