#### **6.3.2. Study visits (Weeks 0, 4, 8, 12, 16, 20 and 24, a total of 7 study visits)**

At each visit, study personnel will do anthropometric measurements (weight and waist circumference), take their blood pressure, collect the beverage logs and provide new beverage logs. They will also do case report forms, medication and supplement list, medical history form, physical activity questionnaire, symptoms checklist, control eating questionnaire and provide participants with the study beverages. Participants will receive motivational phone calls every 2-weeks between visits to provide reminders and ensure fidelity to the protocol.

At weeks 0, 12 and 24, adherence biomarkers in blood and urine samples will be collected and participants will do the diet quality assessment (Diet ID). Study personnel will obtain the 24-hour urine collection from participants at the study visits. A registered nurse will collect the blood sample, at weeks 0 and 24 at the time of the OGTT blood collection, and at week 12, the blood sample collection will be done by a single venipuncture. Participants will be given a unique user and visit code (for weeks 0, 12 and 24) number for logging in to the Diet ID [41] website.

At weeks 0 and 24, participants will have the following assessed/collected:  $^1\text{H}$ -MRS (IHCL, IMCL), the 75g-OGTT (glucose tolerance, indices) [63], blood samples (lipids, liver enzymes, etc), fecal samples (microbiome), and diet quality (Harvard Willett FFQ). The  $^1\text{H}$ -MRS will be performed to measure ectopic fat in liver and calf muscles. Participants will have the  $^1\text{H}$ -MRS at the CFI-funded MRI Research Unit at St. Michael's Hospital and will continue their visit at the Clinical Nutrition and Risk Factor Modification Centre located also at St. Michael's Hospital. Participants will come in to the study site in a 10 to 12-hour fasted state. They will be instructed to maintain the same dietary and exercise patterns the evening before each test and to consume a minimum of 150g of carbohydrate each day over the three days prior to the test. To ensure that these instructions are followed, participants will be provided with examples of what constitutes 150g of carbohydrate. A fasting blood sample for secondary, exploratory and adherence outcomes (including glucose, insulin, lipid panel, ALT and other liver enzymes, and other

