### 7.3. Other Pre-specified outcomes

- Ectopic muscle fat  
IMCL in calf muscles by  $^1\text{H}$ -MRS measured at weeks 0 and 24  
[Time Frame: End value at week 24]
- MetS criteria: waist circumference  
Waist circumference measured at weeks 0, 4, 8, 12, 16, 20 and 24  
[Time Frame: End value at week 24]
- MetS criteria: FPG  
Fasting plasma glucose concentration measured at weeks 0 and 24

[Time Frame: End value at week 24]

- MetS criteria: Triglycerides  
Fasting serum triglycerides concentration measured at weeks 0 and 24  
[Time Frame: End value at week 24]
- MetS criteria: HDL-C  
Fasting serum HDL cholesterol concentration measured at weeks 0 and 24  
[Time Frame: End value at week 24]
- MetS criteria: SBP  
SBP measured at weeks 0, 4, 8, 12, 16, 20 and 24  
[Time Frame: End value at week 24]
- MetS criteria: DBP  
DBP measured at weeks 0, 4, 8, 12, 16, 20 and 24  
[Time Frame: End value at week 24]
- MetS Reversion  
Reversion to <3 of 5 IDF/NHLBI/AHA/WHF/IAAS/IASO MetS criteria measured at weeks 0 and 24  
[Time Frame: End value at week 24]
- Diabetes Incidence  
Incidence of diabetes (Diabetes Canada 2018 FPG and 2h-PG [75g-OGTT], or HbA1c criteria) measured at week 24  
[Time Frame: End value at week 24]
- Body weight  
Body weight measured at weeks 0, 4, 8, 12, 16, 20 and 24  
[Time Frame: End value at week 24]
- Microbiome diversity  
Gut microbiome composition by 16S rRNA sequencing measured at weeks 0 and 24  
[Time Frame: End value at week 24]
- NAFL markers - ALT  
Serum ALT concentrations measured at weeks 0 and 24  
[Time Frame: End value at week 24]
- NAFL markers - AST  
Serum AST concentrations measured at weeks 0 and 24  
[Time Frame: End value at week 24]

- NAFL markers - GGT  
Serum GGT concentrations measured at weeks 0 and 24  
[Time Frame: End value at week 24]
- NAFL markers - ALP  
Serum ALP concentrations measured at weeks 0 and 24  
[Time Frame: End value at week 24]
- NAFL markers – FLI  
FLI measured at weeks 0 and 24  
[Time Frame: End value at week 24]
- Hepatic insulin resistance - HOMA-IR  
Homeostatic model assessment of insulin resistance (HOMA-IR) measured at weeks 0 and 24  
[Time Frame: End value at week 24]
- Uric acid  
Serum uric acid measured at weeks 0 and 24  
[Time Frame: End value at week 24]
- Established lipid targets - LDL-C  
Serum LDL-C measured at weeks 0 and 24  
[Time Frame: End value at week 24]
- Established lipid targets - non-HDL-C  
Serum non-HDL-C measured at weeks 0 and 24  

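### Section 11 promises a relative risk for diabetes incidence from a logistic model without saying how, and its generic baseline covariate carries no usable information for the two binary outcomes

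*Protocol*

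**What the plan says.** Section 11 (Statistical Analysis) gives one rule for outcomes that are not continuous: "logistic regression models for categorical data (odds ratio with 95% CI for MetS reversion and relative risk with 95% CI for diabetes incidence". It applies one adjustment set to continuous and binary outcomes alike: age, sex, NAFLD status, medication use, "intervention dose (servings/day), and baseline level of the end value". It gives no separate baseline term for the binary outcomes and restricts neither analysis to participants who could have the event. The stated approach is intention to treat with inverse probability weighting.

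The outcomes are defined in Table 1 and Section 7.3:

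- **MetS reversion**: "Reversion to <3 of 5 IDF/NHLBI/AHA/WHF/IAAS/IASO MetS criteria measured at weeks 0 and 24".
- **Diabetes incidence**: "Incidence of diabetes (Diabetes Canada 2018 FPG and 2h-PG [75g-OGTT], or HbA1c criteria) measured at week 24".

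On who is at risk at week 0:

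- The Protocol Summary describes the population as "Overweight/obese participants with MetS who are consuming" at least one SSB a day. The inclusion list in Section 5.1 requires BMI, waist circumference and SSB intake. It does not require three or more MetS criteria.
- Section 5.2 excludes diabetes, with the note "Disease exclusions will be based upon self-reported diagnosis".
- Section 6.3.2 schedules the OGTT and fasting bloods at both ends of the trial ("At weeks 0 and 24, participants will have the following assessed/collected"), so week-0 glycaemia and the other MetS components will be on file.

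**The concern.** There are two separate problems.

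1. **Effect measure.** The protocol fixes both the model and the reported measure for diabetes incidence, and the one is not the direct output of the other. An analyst must choose a conversion after the data are in, or risk labelling an exponentiated coefficient as a relative risk. An odds ratio always lies further from 1 than the relative risk, so that label would overstate the effect.

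2. **Baseline covariate.** Adjusting for the baseline value makes sense for liver fat or weight. For an event that can happen only to people who start in one state, the baseline state is the same for everyone who can have it. The covariate then does nothing, while informative week-0 measures stay out of the model. If people not at risk are left in, the outcomes themselves become unclear. Someone without MetS at week 0 cannot revert, and someone with undiagnosed diabetes at week 0 could be counted as an incident case at week 24.

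**Working it through.** **Inputs.** From the protocol: 62 per arm and 20% attrition (Section 4.3), so 62 × 0.8 = 49.6, about 50 completers per arm. Event rates are not given, so all rates below are assumptions. Section 11 states no figure on this point to reproduce, and the sample size is not affected.

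**Step 1: how far the odds ratio is from the relative risk.** With control risk p and relative risk RR,

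OR = [RR·p / (1 − RR·p)] / [p / (1 − p)].

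Worked example, p = 0.10 and RR = 2: OR = (0.20/0.80) / (0.10/0.90) = 2.25, and 2.25/2 = 1.125.

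| Assumed control risk | RR 0.5: OR | Difference | RR 2: OR | Difference |
|---|---|---|---|---|
| 2% | 0.495 | −1.0% | 2.04 | +2.1% |
| 5% | 0.487 | −2.6% | 2.11 | +5.6% |
| 10% | 0.474 | −5.3% | 2.25 | +12.5% |

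**Step 2: can the logistic model give a relative risk?** Yes, with an extra step. In a large simulated sample with control risk near 30% and true RR 1.5, the exponentiated coefficient was 2.05. Averaging the same model's predicted risks under each treatment and taking their ratio (marginal standardisation) gave 1.51. With control risk near 10% and true RR 0.5, the two figures were 0.476 and 0.511.

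**Step 3: the baseline term.** There are two ways to read it as binary status.

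- *Restricted to those at risk* (MetS at week 0; no diabetes at week 0): the column is constant and collinear with the intercept. A design matrix of intercept, two arm indicators, age and this column has rank 4 for 5 columns. The term drops out and the other covariates stay.
- *Unrestricted, for reversion*: participants without MetS at week 0 cannot have the event. Coded as non-events, they are predicted perfectly and the term has no finite estimate. Coding them as events because they have fewer than three criteria at week 24 would measure week-24 status, not reversion.

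**Step 4: what a useful baseline covariate would add for reversion.** Simulated two-arm comparison, 4,000 runs per row, logistic model, two-sided 0.05. Assumed: reversion 21% against 39%; 50%, 30% and 20% starting with 3, 4 and 5 criteria. The slope is the assumed change in log odds of reversion per extra criterion at week 0.

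| Per arm | Slope | Power, no baseline count | Power, with count | Gain (points) |
|---|---|---|---|---|
| 50 | −0.5 | 48.6% | 50.6% | 2.0 |
| 50 | −1.0 | 48.4% | 53.2% | 4.8 |
| 50 | −1.5 | 49.1% | 57.7% | 8.6 |
| 62 | −0.5 | 57.8% | 59.4% | 1.6 |
| 62 | −1.0 | 59.0% | 63.5% | 4.5 |
| 62 | −1.5 | 58.9% | 66.3% | 7.4 |

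The gain is roughly 2 to 8 points, with about 1 point of simulation error on each power figure. A still steeper slope of −2 gave 11 to 12 points, so the figure depends on an assumption the protocol cannot supply.

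**Step 5: how many diabetes events to expect.** With about 50 per arm, a control risk of 10% and 5% in each milk arm, the total is 5 + 2.5 + 2.5 = 10 events. At 5% and 2.5% it is 2.5 + 1.25 + 1.25 = 5. The planned model has two treatment terms and at least six covariate terms.

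**The case against.** The strongest reply has four parts.

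- **A relative risk can be had from a logistic fit.** The sentence names the odds ratio and the relative risk separately, so the authors know the difference. This stands: the protocol does not say that an odds ratio will be presented as a relative risk, and a reader should not infer that it will be. What remains is that the step between model and measure is not stated, although both ends are fixed.

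- **Baseline status is not constant across everyone randomised.** This also stands. A reader might infer that all participants start with MetS and without diabetes. The documents do not support that: diabetes is excluded by self-report only, and no listed criterion requires three MetS components. It does not rescue the covariate, which is constant among those at risk and meaningless for those who are not. It also shows that the at-risk set needs defining.

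- **The phrase could mean the underlying measures**, such as FPG or the number of criteria, with coding left to an analysis plan. That is possible. But the same section names baseline FPG and 2h-PG for subgroups and does not name them for adjustment, so the text does not settle it.

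- **The suggested models may be fragile with few events.** This is right for diabetes (Step 5) and limits how many covariates the fix should carry.

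**Conclusion.** The point holds and is minor. The model and the effect measure do not match for diabetes incidence. If the exponentiated coefficient were used, it would be off by about 3% to 12.5% at assumed control risks of 5% to 10% and a true relative risk of 0.5 or 2, and by 1% to 2% at a control risk of 2%. The baseline term carries no usable information for either binary outcome. The cost is precision and clarity, not bias: a constant covariate drops out and the remaining adjustments still work. For reversion the forgone gain is roughly 2 to 8 points of power at 50 to 62 per arm, under assumed prognostic slopes.

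Two stronger readings are not supported. The odds ratio for MetS reversion is not an error: it is what a logistic model estimates, and preferring a risk ratio there is a matter of reporting taste. Nor does the point reach the primary or secondary results, since both outcomes are listed in Section 7.3 as other pre-specified outcomes and no sample size or primary test depends on them.

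**What to change.** In Section 11, or in the analysis plan if it governs:

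1. **Diabetes incidence, effect measure.** State that the relative risk and 95% CI come from marginal standardisation of the logistic model or from modified Poisson regression with robust standard errors. Alternatively, report an odds ratio. Keep covariates few if events are sparse, and say in advance which are kept.
2. **At-risk sets.** Analyse reversion among participants with three or more MetS criteria at week 0, and incidence among those without diabetes on the week-0 tests. Both restrictions use baseline data, so the randomised comparison is kept within the subset. Report how many are excluded by arm.
3. **Baseline covariate.** For these two outcomes, replace the generic baseline term with the week-0 number of MetS criteria (reversion) and week-0 FPG or 2h-PG (diabetes).
4. **MetS reversion.** The odds ratio can stay.

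The cost is a few sentences. No new data are needed and the sample size does not change. The at-risk restriction may remove some participants from these two analyses; the protocol gives no basis for saying how many.
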